### Randomization

After the baseline survey is administered, the biostatistician will use SAS (SAS Institute) to perform a permuted stratified blocked randomization [33]. The stratification variable used maintenance therapy versus no maintenance therapy. The rationale for this stratification is that those patients with ovarian cancer who receive maintenance therapy with a poly (ADP-ribose) polymerase (PARP) inhibitor may experience a different symptom burden or illness trajectory that impacts outcomes [3]. Survivors will be randomly allocated to either the control group or the POSTCare intervention group with a 1:1 ratio (N=120). Stratification will be based on disease stage and maintenance therapy (a PARP inhibitor vs Bevicizumab vs no maintenance). Each of these factors is associated with overall QOL and symptom burden. Participants, clinicians, data collectors, biostatisticians, and investigators will be blinded to allocation. The research nurse interventionist (described below) will not be blinded but will not conduct study activities related to measuring, collecting, or interpreting outcomes. Although this is a low-risk intervention, unblinding decisions will be made by the investigators in the context of serious adverse events attributable to the study. If a decision is made to unblind a participant, the study data coordinating center will undertake the unblinding and protect the confidentiality of treatment assignments for other participants. The treatment assignment will be communicated to the participant and the participant’s treating physician. The unblinding event will be reported to the Baylor College of Medicine institutional review board, documented in trial records, and the analysis of study outcomes may be adjusted to account for the unblinded participant to ensure that the integrity of the overall trial results is maintained. Criteria for study dropout include withdrawal of consent, failure to adhere to protocol, loss to follow-up, health changes making further participation burdensome, and personal reasons or changes in life circumstances.

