**Predictor variables**					
	Demographic or medical information		Demographic questionnaire: will include gender, race, and treatment history	N/A^b^	Electronic medical record
	Cancer coping style		Brief version of the Coping Orientation to Problems Experienced [57]	.75	Patient self-report
	Social support		Social Provisions Scale [58]	.92	Patient self-report
	Education level		Stanford Education [59]	N/A	Patient self-report

^a^Not available.

^b^N/A: not applicable.

“Aim 2” applies mediation analysis to the data acquired from the RCT proposed in Aim 1. Aim 2 explores the potential for heterogeneity in the effectiveness of the POSTCare survivorship program. The primary end point for aim 2 is QOL at 6 months, as measured by the FACT-O. Combining both study arms, subgroup analysis will assess the distributions of potential prognostic factors for QOL at 6 months. Analyses will adjust for statistically significant prognostic factors. Mediation modeling will be applied to decompose the relationships among the care plans, intermediate surrogate markers of QOL acquired during the course of follow-up, and QOL at 6 months. Surrogate markers include patient activation, goal setting, self-efficacy, and care satisfaction, to be collected at 12 weeks and 24 weeks from surveys identified in Table 1. For each surrogate marker, an intermediate response will be defined. The direct and indirect impact of POSTCare will be estimated for each surrogate response using mediation analysis [60-62] to elucidate the causal mechanisms of QOL and assist with planning for larger confirmatory studies and studies in other disease types.

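### Aim 2 picks its adjustment covariates by statistical significance in the trial's own data, which is not a criterion for mediator-outcome confounding; a fixed set would be better and costs almost nothing

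*Protocol article*

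**What the plan says.** The Aim 2 paragraph (Methods, Outcome Measures, after Table 1) "applies mediation analysis to the data acquired from the RCT proposed in Aim 1". Its outcome is fixed: "The primary end point for aim 2 is QOL at 6 months, as measured by the FACT-O". The covariates are chosen in two steps. First, "Combining both study arms, subgroup analysis will assess the distributions of potential prognostic factors for QOL at 6 months". Then, "Analyses will adjust for statistically significant prognostic factors". The mediation models that follow, for patient activation, goal setting, self-efficacy and care satisfaction, are meant "to elucidate the causal mechanisms of QOL and assist with planning for larger confirmatory studies".

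Two other places bear on the rule. The Randomization section says of disease stage and maintenance therapy: "Each of these factors is associated with overall QOL and symptom burden". The predictor block of Table 1 has four rows: demographic or medical information ("Demographic questionnaire: will include gender, race, and treatment history"), coping style ("Brief version of the Coping Orientation to Problems Experienced"), social support and education. FACT-O is listed once in that table, as a primary outcome. The text of Outcome Measures says it is also collected at baseline.

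No covariate is named as always included in the Aim 2 models, and no significance threshold is given.

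**The concern.** Randomisation protects the comparison of arms. It does not protect the path from mediator to QOL, because women are not randomised to a level of activation or self-efficacy. That path has a causal reading only if common causes of mediator and outcome are adjusted for. Whether a factor is such a cause depends on its relation to both variables. A significance test against the outcome looks at one side only, and its result depends on the sample size. Screening on the outcome that is then modelled also means that ordinary standard errors ignore the selection step, and that the adjustment set can change by chance.

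The rule also sits badly with the article's own statement on stage and maintenance therapy. Having described them as associated with QOL and stratified on them, it would keep them in Aim 2 only if they reach significance again.

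At stake is the reading of the mediators. The abstract says they will guide revision of the intervention, and the Aim 2 paragraph says they will help to plan later studies. A mediator that looks active only through confounding would misdirect both.

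**Working it through.** **Inputs from the article.** N = 120, 60 per arm; outcome 6-month FACT-O; screen on pooled arms. Aim 2 states no figure to reproduce. The only power statement (at least 80% for 8 points) concerns the Aim 1 comparison and does not bear on this point.

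**Assumptions (the article gives none of these).** Screening threshold p < 0.05. All correlations below. An arm effect on the mediator of 0.5 SD, unless stated otherwise. True effect of mediator on QOL zero, so every significant path is false. Linear models for mediator and outcome.

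**Step 1: how often the screen keeps a factor.** For correlation r with the outcome, the chance of reaching p < 0.05 is about Φ(atanh(r)·√(N − 3) − 1.96), with √117 = 10.82.
- r = 0.15: 0.1511 × 10.82 = 1.63; Φ(−0.33) = 0.37, so dropped in 63% of trials.
- r = 0.20: 0.2027 × 10.82 = 2.19; Φ(0.23) = 0.59, so dropped in 41%.
- r = 0.50: 0.5493 × 10.82 = 5.94; Φ(3.98) > 0.999, so practically never dropped.

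The screen loses weak factors about half the time and keeps strong ones.

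**Step 2: what an omitted confounder does.** With the mediator scaled to unit variance within arm, the spurious mediator coefficient is the product of the confounder's correlations with mediator and outcome.
- Weak factor: 0.4 × 0.20 = 0.08 SD per SD.
- Strong factor: 0.4 × 0.50 = 0.20. Its standard error is about √((1 − 0.20²)/117) = 0.0906, so 0.20/0.0906 = 2.21 and Φ(2.21 − 1.96) = 0.60. The path is falsely significant in about 60% of trials.

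**Step 3: the rule as a whole, by simulation (2,000 to 4,000 trials per setting, N = 120).** The last two columns give the share of trials with a falsely significant mediator-to-QOL path.

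| Setting | Dropped by screen | With screen | Fixed adjustment |
|---|---|---|---|
| One confounder, r 0.20 with outcome, 0.3 to 0.4 with mediator | about 41% | about 5% (4.9% to 5.8%) | about 5% (4.6% to 5.4%) |
| Three confounders, r 0.15 to 0.20 with outcome, 0.3 to 0.4 with mediator | each about 40% to 63% | 9% to 12% | 4% to 6% |
| Baseline FACT-O among the candidates, r 0.5 to 0.6 with outcome, 0.2 to 0.4 with mediator | never | about 5% | about 5% |

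With one weak confounder the mean spurious coefficient after screening is about 0.013 to 0.020, well below 0.06 to 0.08 (0.3 × 0.20 to 0.4 × 0.20). The trials that drop the factor tend to be those in which its sample correlation with the outcome happens to be small.

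**Step 4: if baseline FACT-O were never a candidate.**
- Four screened proxies, each correlated 0.4 with baseline FACT-O: false mediator-to-QOL path in 10% to 40% of trials. Both paths are significant in 4% to 39%, as the arm effect on the mediator goes from 0.3 to 0.8 SD and the correlations vary.
- No proxy adjusted for, r 0.4 with mediator and 0.5 to 0.6 with outcome: false path in 60% to 75%.

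With 96 women (120 × 0.8, an assumed 20% loss) the pattern is the same.

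**The case against.** A reader might infer from Table 1 that baseline FACT-O is left out of the Aim 2 models, and so that false mediation is common. The article does not support this. The Aim 2 paragraph never limits the candidate factors to the predictor block. Outcome Measures describes the remaining measures as serving both as secondary outcomes and as possible predictors, and it uses baseline FACT-O as a predictor of progression-free and overall survival. Table 1 lists instruments and has no baseline row for any of them. If baseline FACT-O is a candidate, the screen keeps it essentially always. The large percentages in Step 4 therefore describe an analysis that the article does not state.

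A reader might also call stage and maintenance therapy known mediator-outcome confounders. The Randomization section links them to QOL and symptom burden. It says nothing of activation, goal setting, self-efficacy or care satisfaction, so the mediator side is not established.

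Further, Aim 2 is exploratory, and the article concedes under its limitations that its capacity to evaluate mediators is constrained. Detailed covariate lists are commonly left to a full protocol or analysis plan, which is not at hand.

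The first two objections stand and limit the size of the point. The last stands only in part. The article does not leave the covariates open: it fixes a rule, and a plan that follows it inherits the weakness.

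**Conclusion.** The point holds in a limited form. Significance against 6-month FACT-O is the wrong basis for choosing covariates in a causal mediation model. The rule allows factors that the article itself ties to QOL to drop out by chance, and it leaves adjustment for baseline FACT-O unspecified. Under the assumed correlations the screen alone raises false mediator-to-QOL findings from about 5% to at most about 12%, and hardly at all with a single weak confounder. Serious inflation needs the further condition that baseline FACT-O is never considered, which the text neither states nor excludes. All these figures depend on correlations that the article does not give. The 12-week primary comparison is untouched. This is a cheap improvement to an exploratory aim.

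**What to change.** Replace the significance sentence with a pre-specified set. Every Aim 2 mediator model and outcome model includes arm, baseline FACT-O, the baseline value of the mediator where it is collected, and the randomisation factors (stage and maintenance therapy), whatever their p-values. Name any further Table 1 covariates (such as coping style, social support or education) in advance, or keep them for a labelled sensitivity analysis. Drop p-value screening.

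The cost is one sentence and a few degrees of freedom out of 120. Baseline FACT-O is already collected, and stage and maintenance therapy must be known in order to stratify. Fixing the set before results are seen also settles whether baseline FACT-O is adjusted for, on which most of the potential bias depends.

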## Methods

### Study Design

We will conduct a 2-arm RCT to evaluate the impact of a telehealth-delivered survivorship transition care platform. Survivors of ovarian cancer (N=120) will be randomly allocated to receive survivorship care either using the POSTCare Platform or standard of care. Study design and reporting will be in accordance with the CONSORT (Consolidated Standards of Reporting Trials) checklist. We will use quantitative and qualitative methodologies in a concurrent triangulation mixed methods design using qualitative data to augment our interpretation of quantitative data. Outcomes will be collected at baseline, 12 weeks, and 24 weeks, with the primary outcome being a QOL assessment at 12 weeks after the survivorship transition (Figures 2 and 3).

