### Control Group

The control group will receive standard survivorship care delivered through telehealth. All sites have a standard survivorship visit that includes the use of a software package to generate the delivery of a paper SCP based on American Society of Clinical Oncology guidelines. This comprises a treatment summary, an upcoming surveillance visit schedule, and guidance on late effects. This visit includes the delivery of information and specifically does not include goal setting, use of the dual framework technique (described in the “Intervention” section), acceptance and commitment intervention (described in the “Intervention” section), self-management coaching, or the use of motivational interviewing techniques. To ensure fidelity to control group standards, all visits will be audio-recorded and reviewed to evaluate for evidence of contamination of the control condition. Telephone-based booster contacts will serve as attention control with structured delivery of educational material on surveillance visits and bone health.

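### Aim 2 lists goal setting as a mediator with no measure and no planned overlap between arms, picks covariates by significance, and leaves the mediator wave open

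*Protocol article*

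**What the plan says.** All from the protocol article, Methods.

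- **Outcome Measures, Aim 2 paragraph (after Table 1).** "The primary end point for aim 2 is QOL at 6 months, as measured by the FACT-O". Mediation modelling is to decompose the relation between care plan, "intermediate surrogate markers of QOL acquired during the course of follow-up", and that outcome. The stated purpose is to learn about causal mechanisms and to help plan larger studies.
- **Same paragraph, mediators.** "Surrogate markers include patient activation, goal setting, self-efficacy, and care satisfaction, to be collected at 12 weeks and 24 weeks", with the surveys in Table 1 named as their source. An intermediate response is to be defined for each marker; no wave is named.
- **Same paragraph, covariates.** "Analyses will adjust for statistically significant prognostic factors".
- **Study Design.** "Outcomes will be collected at baseline, 12 weeks, and 24 weeks". The 6-month outcome is therefore the 24-week survey.
- **Control Group.** The standard visit "specifically does not include goal setting", and recordings are reviewed for contamination.
- **Patient-Centered Design.** Identifying health goals is described as the central activity of POSTCare.
- **Table 1.** Instruments are listed for self-efficacy, patient activation, and satisfaction with communication and care coordination. None is listed for goal setting.

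**The concern.** A mediation analysis needs three things that this paragraph does not secure.

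1. The mediator must be measured, and must be able to vary within each arm. Goal setting has no listed instrument, and as a delivered element it is present in one arm and barred from the other.
2. Confounders of the mediator-outcome relation must be adjusted for, because randomisation balances arms but not mediator levels within arms. A significance rule selects on the association with outcome in a small sample, not on confounding.
3. The mediator should precede the outcome. A marker answered at the 24-week survey has no time order relative to FACT-O at that survey, and all of these are self-report.

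The Abstract says that the mediators found will inform revision of the intervention. The practical risk is that a component is kept or strengthened because of an indirect effect that the data could not show.

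**Working it through.** The plan states no figure for Aim 2, so there is none to reproduce. Inputs from the protocol are N=120, 60 per arm, and follow-up surveys at 12 and 24 weeks. All correlations, proportions and effect sizes below are assumptions.

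**Goal setting against arm.** Let p_c and p_t be the proportions with goal setting in control and POSTCare, and p their mean. With 1:1 allocation, corr = 0.25(p_t − p_c)/√[0.25·p(1−p)] and VIF = 1/(1 − corr²).

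| control / POSTCare | corr | VIF | controls with a goal (of 60) |
|---|---|---|---|
| 0% / 100% | 1.00 | infinite | 0 |
| 0% / 90% | 0.905 | 5.5 | 0 |
| 20% / 90% | 0.704 | 2.0 | 12 |
| 40% / 90% | 0.524 | 1.4 | 24 |

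In the first row, the design matrix (intercept, arm, goal setting) has rank 2 of 3, so direct and indirect effects cannot be separated. In the second row, the goal-setting coefficient comes only from the 6 POSTCare women without a goal (60 × 0.10) against the other 54, and nothing is learned about goal setting under control. The lower rows apply only if goal setting is measured as the woman's own behaviour, for which Table 1 has no instrument.

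**Significance rule.** At N=120 and an assumed two-sided 0.05 level (t = 1.980 on 118 df), an observed correlation with FACT-O must exceed 1.980/√(118 + 1.980²) = 1.980/11.04 = 0.18 to be selected. A factor with a true correlation of 0.18 is therefore missed about half the time, however strongly it relates to the mediator.

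**24-week marker as mediator.** Suppose there is no mediation and the marker only reflects same-survey QOL: Y = τA + e and M = rY + √(1−r²)·e₂, with unit variances. Then:

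- effect of arm on marker: a = rτ
- coefficient of marker given arm: b = r
- indirect/total = (rτ·r)/τ = r²

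This gives 16%, 25% and 36% at r = 0.4, 0.5 and 0.6. Simulation with N=400,000 gave 0.160, 0.247 and 0.358.

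A second simulation used n=120, 3,000 runs and a total effect of 0.5, with the 24-week marker depending on both its 12-week value and 24-week QOL. With a true indirect effect of 0 and QOL-to-marker paths of 0.2, 0.4 and 0.6, the 24-week marker gave 0.075, 0.172 and 0.266, or 15%, 34% and 53% of the total. The 12-week marker gave about 0.00. With a true indirect effect of 0.15, the 12-week marker gave 0.148 to 0.150. That result assumes no mediator-outcome confounding.

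**Limit of the 12-week marker.** If 12-week QOL drives the 12-week marker and carries forward to week 24 with within-arm correlation ρ, then a = rτ and b = rρ. The spurious share is r²ρ, assuming equal effects at both waves and no baseline adjustment. At r = 0.5 and ρ = 0.7 this is 0.25 × 0.7 = 17.5%, against 25% for the 24-week marker.

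**The case against.** **Wave.** A reader might infer that Aim 2 has chosen 24-week mediators, or that its whole causal decomposition is unidentified. The text supports neither. Naming 12 and 24 weeks is the ordinary survey schedule, the markers are called intermediate, and their definition is deferred. The 12-week reading is natural, and the choice may be fixed in a fuller plan. For activation, self-efficacy and care satisfaction at week 12 the time order is right, and identification rests on the usual assumption of no unmeasured mediator-outcome confounding. What stands is that the sentence permits the 24-week use, so the r² figures describe that reading only. They also assume a product-of-coefficients estimate, which the article does not name.

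**Goal setting.** The protocol bars goal setting from the control visit; it does not say that control women set no goals of their own. That is fair, and the collinearity eases quickly once they do. But a patient-level measure would be needed, and the stated source has none.

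**Heterogeneity.** The paragraph says that "Aim 2 explores the potential for heterogeneity in the effectiveness of the POSTCare survivorship program", then pools the arms to study prognostic factors. A reader might infer that the pooled analysis is offered as a test of effect modification. It is presented only as a study of prognosis that feeds the adjustment set, and elsewhere Aim 2 is described in terms of mediators or associated factors. The wording is loose, and interaction tests at N=120 would be a preference rather than a correction.

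**Stakes.** Aim 2 is exploratory, and the Discussion concedes limited ability to evaluate mediators. This lowers the severity, although the limits are put down to recruitment and budget rather than to timing or overlap.

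**Conclusion.** The point holds in three parts of unequal strength.

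- **Firm:** goal setting is named as a Table 1 marker with no Table 1 measure. As a delivered component withheld from control, its direct and indirect effects cannot be separated.
- **Firm as a stated rule, size unknown:** choosing adjustment factors by significance is a poor safeguard for the mediator-outcome path at N=120.
- **Conditional:** because the wave is left open, a 24-week marker could be used. If it were purely a consequence of same-survey QOL, 16% to 36% of the total effect would be wrongly credited to it at assumed r of 0.4 to 0.6.

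Moderate for what Aim 2 may claim about mechanism, minor for the trial as a whole. The Aim 1 primary analysis is unaffected.

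**What to change.** In the Aim 2 paragraph:

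1. Remove goal setting from the formal mediators and describe it within the POSTCare arm. Alternatively, add to Table 1 a patient-level measure that can vary in both arms.
2. Name the 12-week activation, self-efficacy and care-satisfaction scores as the mediators of 24-week FACT-O, and treat the 24-week scores as secondary outcomes.
3. Replace the significance rule with a fixed list: baseline marker, baseline FACT-O, randomisation strata as actually used (the Randomization section describes them in two ways) and site.
4. State that residual mediator-outcome confounding, including by 12-week QOL, remains possible.

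The cost is wording and analysis code, plus the loss of the 24-week markers and, unless a measure is added, goal setting as formal mediators. One condition needs checking. Study Design puts outcomes at baseline, but the Aim 2 sentence names only weeks 12 and 24 for the markers. If baseline marker scores were not collected, baseline FACT-O has to carry more of the adjustment and the caveat in item 4 becomes stronger.

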### Ethical Considerations

Ethical approval for this trial has been obtained through the Baylor College of Medicine Institutional Review Board (H52939). All participants in the trial will provide informed consent before the initiation of study activities. The primary risk in this study is a risk to confidentiality. All study data will be uploaded directly to the data coordinating center, REDCap (Research Electronic Data Capture; Vanderbilt University), which is implemented to be compliant with HIPAA (Health Insurance Portability and Accountability Act) standards. Participants will receive compensation for their participation in the trial in a longitudinal manner, with US $10 at baseline and 12 week data collection timepoints and US $30 at the 24 week time point. Total participant compensation is US $50.

